***Implementation Outcomes***

Initial analyses will include examination of measure distribution, tests of normality, and confirmatory factor analysis, to create multi-indicator, multi-informant constructs where appropriate. Reach: Effect sizes of differences between 1) the study sample and clinic population, and 2) those who were eligible and enrolled vs. those who were eligible and declined will be determined by descriptive comparisons of multiple sociodemographic characteristics, including race/ethnicity, maternal age, child gender, and income. Fidelity: Summary scores will be created for fidelity data across sessions (i.e., computing proportion of HS and/or VIP session components completed on average, and the interquartile range). Scores will be computed separately for VIP (PCEs related) and HS (ACEs related) content for component analysis to understand whether differential implementation outcomes/challenges occur when HS+VIP is implemented jointly. Engagement: Chi-square tests for independence will be used to examine differences between the proportion of visits attended in the HS+VIP and standard HS models.

Acceptability: To investigate acceptability among parent participants, SEM will be used to examine AIM scores across assessment timepoints and to examine whether trajectories in parent AIM scores vary by participation or sociodemographic characteristics. In addition, multivariate ANOVA will be used to examine acceptability across interested parties at different levels (parents, HS+VIP care team). Finally, confirmatory factor analysis will be used to create a multi-informant acceptability construct and multivariate ANOVA will again be used to examine differences in overall acceptability across HS+VIP and standard HS groups.

Appropriateness: Analysis of appropriateness will mirror analyses used to examine acceptability.

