## Study Endpoints

### Primary Study Endpoints

Parent mental health, parenting practices, parent-child interaction, parent-child relationship, social determinants of health, child development, intervention feasibility, acceptability, reach, and participant engagement. These outcomes will be measured through surveys, interviews, parent-child observations, and direct assessments of child development (see Section 6 for additional details on specific measures).

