### Administration of Intervention

The combined HS+PlayReadVIP model is delivered in person or online with 9 structured sessions from infant age 4 months to 36 months, coinciding with pediatric well-child visits. The program is delivered by trained HS Specialists, with a Masters’ degree or higher. Training ensures fidelity, and sessions are tailored to family needs with flexible scheduling. This approach integrates behavioral and social strategies into pediatric care, minimizing disruption to families and providers.

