## Sample Size

Sample size was estimated based on a cumulative attrition rate of 15-20% by 24M, similar to previous studies of PlayReadVIP in New York City, and a conservative effect size of HS+PlayReadVIP for main impact analyses of *d* = .30. This effect size is below previous studies of PlayReadVIP alone (*d* = .3-.5), accounting for the potential for non-additive impacts of HS+PlayReadVIP following integration with standard HS. With enrollment of 500 families, we expect a final sample size of 400, which provides more than 80% power to detect an effect size of *d* = ~.3 given alpha = .05 in ANOVA analyses,^166^ a small-to-medium effect size of *f^2^*=.04 in our most complex OLS regression analyses including moderation, and β*_YX_* = 0.3, with only moderate item reliability^167^ in SEM analyses. Our final sample of 400 will provide 80% power to detect a small-to-medium effect size (.26) in mediation analyses based on previous simulation studies.^168^ Analysis of fidelity of delivery will be based on number of sessions (~1125-1500, or 7-10 sessions per family over 2 years), rather than number of families. We have 80% power to detect a small effect size of β*_YX_* = 0.1 in these SEM models.^167^

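### The engagement comparison does not make the family the unit; on its natural reading, the chi-square test on visits attended ignores within-family correlation and its p-values are too small.

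*Protocol*

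**What the plan says.** The Engagement entry in the Protocol, Statistical and Analytical Plans, Implementation Outcomes, reads: "Chi-square tests for independence will be used to examine differences between the proportion of visits attended in the HS+VIP and standard HS models". It does not mention clustering, a robust variance, a GEE or a mixed model, and it does not name the unit of analysis.

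Related statements elsewhere in the protocol:

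- **Unit of randomisation.** The Protocol Summary and Randomization Procedures assign families (dyads) to the two arms.
- **Visits per family.** Sample Size gives "7-10 sessions per family over 2 years", in a sentence about fidelity. Administration of Intervention gives "9 structured sessions from infant age 4 months to 36 months".
- **Status of engagement.** Primary Study Endpoints ends its list with "acceptability, reach, and participant engagement".
- **The neighbouring outcome.** Sample Size states: "Analysis of fidelity of delivery will be based on number of sessions", as opposed to families.
- **Other mention of engagement.** Adherence and Retention Analyses tracks sessions attended per participant, but only with summary statistics.

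**The concern.** A chi-square test of independence requires independent observations. Visits are nested within the randomised family: some families come to nearly all of them, some to few, and a family that drops out misses every later one. If visits are pooled, the test uses a variance that is too small by the design effect, and its p-value is too small whenever the within-family correlation is positive.

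What is at stake is the between-arm conclusion on whether adding PlayReadVIP raises or lowers attendance. A chance difference could be reported as real in either direction. The false discovery rate step under Multiple Comparison/Multiplicity does not repair this, because it takes the p-values it receives as valid.

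**Working it through.** **The plan's own power figure.** Sample Size states: "With enrollment of 500 families, we expect a final sample size of 400". For the main comparison it claims power above 80% at d = .3 and an alpha of .05. 500 × 0.80 = 400, and a two-sided comparison of 200 per arm at d = .3 has power 0.85, so the figure reproduces. It concerns the main effect. No power, sample size or ICC is given for engagement.

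**Inputs.**
- Nominal alpha is .05, two-sided (the protocol states no sidedness; a chi-square test is non-directional).
- Visits per family, m, are 7 to 10, borrowed from the fidelity sentence. The 9 sessions under Administration of Intervention lie inside this range.
- A lower range for m is also needed. The fidelity sentence totals about 1,125 to 1,500 sessions. Over one arm of 250 enrolled families that is 1,125/250 = 4.5 to 1,500/250 = 6 each.
- The ICC is assumed, over the range .05 to .5.

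**Formulae.** Design effect DE = 1 + (m − 1) × ICC. True type I error of the unadjusted test = 2 × [1 − Φ(1.96/√DE)].

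Example, m = 7 and ICC = .1: DE = 1 + 6 × .1 = 1.6; 1.96/√1.6 = 1.55; error = .121.

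Example, m = 10 and ICC = .5: DE = 1 + 9 × .5 = 5.5; 1.96/√5.5 = 0.836; error = .403.

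| Assumed ICC | m = 4.5 | m = 6 | m = 7 | m = 10 |
|---|---|---|---|---|
| .05 | 7.1% | 8.0% | 8.6% | 10.4% |
| .1 | 9.2% | 11.0% | 12.1% | 15.5% |
| .3 | 17.1% | 21.5% | 24.2% | 30.8% |
| .5 | 23.7% | 29.5% | 32.7% | 40.3% |

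A threefold error (15%) needs an ICC of about .14 at m = 7, or .095 at m = 10.

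**Check by simulation.** Beta-binomial attendance was simulated with 200 families per arm, mean attendance of 60% or 80% (assumed), m = 7 or 10, and 8,000 runs per setting. The results agree with the formula to within about .01. A t test on each family's number of visits attended had a type I error of .046 to .055 in the same settings.

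**Is a positive ICC plausible?** Sample Size expects 15 to 20% cumulative attrition. Suppose that share of families stops at a random visit, their later visits count as missed, and attendance is otherwise independent at 60 to 90% (assumed). With 250 families per arm and m = 7, 9 or 10, drop-out alone produces an ICC of .07 to .32. The visit-level chi-square then has a type I error of .105 to .323, and the family-level t test .046 to .054. This holds only if visits after drop-out stay in the denominator.

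**The case against.** **The unit is inferred.** The Engagement sentence does not describe a pooled table. It speaks of tests in the plural, and a separate chi-square at each scheduled visit, or one on families grouped by attendance, would be valid. Adherence and Retention Analyses describes engagement per participant, and Sample Size moves only fidelity to the session level, which could suggest that the family is otherwise the unit. This stands in part: pooling is not stated. But the text describes neither valid alternative. A proportion computed per family would be a quantitative score, for which a chi-square test of independence is not suited. The per-participant passage gives summary statistics and does not replace the test.

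**The size is conditional.** A reader might infer that the error is certainly inflated several-fold. The documents do not support that: they give no ICC, and at .05 the factor is only 1.7 to 2.1 with 7 to 10 visits. The visit count is also borrowed, from a sentence whose session total does not fit 7 to 10 sessions for each of 250 families. The 9 sessions run to 36 months of age, whereas Randomization Procedures has delivery through 24 months; those passages need to be reconciled. This objection stands, and it is why the lower range for m is shown.

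**The stakes are limited.** Engagement is an implementation outcome in a Hybrid I design, it appears in neither formal hypothesis, and no sample size or stopping decision depends on it. It is listed as primary, but in a long list that does not rank its constructs. This too stands, and it lowers the priority. The argument that a statistical analysis plan could settle the matter is weaker, because the protocol already names the test and a plan that followed it would keep the problem.

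**Conclusion.** The concern holds in conditional form. The protocol names a test that, on its natural reading, ignores within-family correlation and is anti-conservative for any positive ICC. With 7 to 10 visits per family the nominal 5% becomes roughly 9 to 10% at an ICC of .05 and 33 to 40% at .5; with fewer visits the inflation is smaller but does not vanish. These figures rest on an assumed ICC, a visit count taken from the fidelity sentence, and pooling of visits by arm.

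A reader might go further and conclude that the trial's effectiveness results are compromised. They are not: those analyses use regression and structural equation models on family outcomes, and this point does not touch them. The problem is confined to one implementation comparison and is a should-fix.

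**What to change.** State in the Engagement entry that the family is the unit of analysis. Either of two forms would do:

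- compute each family's attended visits as a proportion of its scheduled visits, and compare arms with a t test or a regression with robust standard errors; or
- fit a logistic GEE or mixed model to the visits, clustered on family.

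In both cases report the between-arm difference in attendance with its 95% CI, and say whether visits after a family withdraws count as scheduled. The simpler family-level t test already brought the simulated error back to about 5%, so a more elaborate model is optional.

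The cost is a sentence of analysis wording. Data collection, sample size and design do not change. The only downside is a wider interval, which reflects the information actually available.

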***Mediation Through Intervention/Health Disparities Theory of Change***

In order to examine whether changes in ECD outcomes at 24M result from program impacts on parents and ERH at 12M, mediation analysis will be used. Analyses will be conducted according to principles set forth by MacKinnon^164^ and Hayes,^165^ using SEM with bias-corrected bootstrapping. Bootstrapping provides an estimate of the sampling distribution of the indirect effect by resampling from the obtained sample with replacement and estimating the path coefficients for each resample. The confidence interval for the indirect effect is calculated from percentile-based lower and upper bounds in the ordered list of the sampling distribution. Confidence interval bounds are bias-corrected to account for skew common in human subjects data.^165^ Mediators will be examined separately, and only mediators on which HS+VIP has a significant impact at 12M will be tested.

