The overarching objective of this protocol, then, is to understand both the effectiveness and practical implementation of the HS+PlayReadVIP model in real-world pediatric primary care environments. Currently, implementing early childhood interventions like HS+PlayReadVIP in pediatric primary care presents several challenges; such as time limitations, limited funding, staffing Issues, lack of training , not reaching the diverse patient polulation and not addressing social determinants directly. This protocol focuses on 2 principle aims that will asses the impact of the integrated HS+PlayReadVIP model on various outcomes : Aim 1: Assess the effectiveness of the HS+VIP model on parent-child relational health, parent mental health, and parenting behaviors compared to standard HealthySteps (HS). And Aim 2: Evaluate the implementation outcomes of the HS+VIP model, including feasibility, acceptability, appropriateness, reach, engagement, and fidelity. Working on these challenges is crucial for the successful implementation and sustainability of early childhood interventions in pediatric primary care settings.

The overall goals are :

1. Aim 1: Determine whether the integrated HealthySteps (HS) and Video Interaction Project (VIP) model has greater impacts on parenting and early child development (ECD) compared to standard HS alone.
2. Aim 2: Understand how and why the integrated HS+VIP model works by examining the mechanisms driving its impacts and the contexts influencing its implementation.

Together, Aim 1 and Aim 2 will:

- Demonstrate the value of integrating evidence-based preventive interventions in pediatric primary care to address disparities in child development.
- Generate actionable knowledge about how to implement and sustain such integrated models effectively in diverse healthcare settings.

By addressing these aims, the study seeks to provide comprehensive insights into both the effectiveness and practical implementation of the HS+VIP model in real-world pediatric primary care environments.

This project will be led by [name], a developmental psychologist with a primary appointment as compensated faculty in the Department of Pediatrics at NYU Grossman School of Medicine.

Primary endpoints: Parenting practices, parent-child relationships and child development.

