*B1. A Key Common Pathway****:*** ERH (Fig. 2), defined as parent-child relationship quality, structuring of the home environment, and responsive/cognitively stimulating practices,^5^ represents a key common pathway by which ACEs and PCEs impact child development.^55^ Importantly, ERH actively promotes skills children need to respond to adversity in a healthy, adaptive manner, including self-regulation, adaptability, and mastery orientation.^56,57^ ACEs negatively affect ERH and ECD through ecological factors and parenting capacities that are barriers to ERH, while PCEs can be considered as both ERH itself and underlying parenting assets that buffer impacts of ACEs and proactively promote ECD and later social and cognitive skills.^9^

*B2. Underlying Frameworks****:*** ERH can be conceptualized as a convergent outcome within two interrelated frameworks with broad theoretical and empirical support (Family Stress and Family Investment models; Fig. 2), supporting its salience as a target for early preventive intervention.^5^

*Family stress model* (FSM):^6^ This posits that inequality of resources and opportunity impact child development^58^ through parent emotional/relational distress^59^ and consequent effects on relationship quality components of ERH (e.g., increased harsh interactions). FSM impacts on ECD (especially child social-emotional competence) are subsequently associated with long-term trajectories of health and well-being (e.g., employment, relationship stability).^36^ The FSM suggests that decreasing ACEs by addressing parent and other psychosocial stressors,^55,60-62^ particularly for families with few resources, can promote ERH and better child outcomes. *Family investment model* (FIM):^7^ This posits that inequality of resources and opportunity impact child development by limiting resources and parent assets, particularly time and money, thereby limiting capacity for provision of learning materials (books, toys), and reducing prospects for 1-on-1 interactions that promote children’s learning skills, with consequent reduction in the responsivity/cognitive stimulation components of ERH (e.g. reading, teaching, and play^16,62-64^). Similar to FSM, FIM impacts on ECD (cognitive, language and social-emotional competence^9,52,65-66^) are associated with long-term trajectories of health and well-being. The FIM suggests that increasing PCEs by supporting ERH and parenting assets can buffer ACEs and enhance outcomes.^68^

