**IV. Evidence-Based Preventive Interventions (EBPIs) Targeting ERH and ECD.**

*A. EBPIs May Address ACEs or Promote PCEs***.** EBPIs are research-based, theory-driven programs that aim to preclude disparities by addressing underlying mechanisms before problems emerge.^69^ There is strong evidence that EBPIs targeting either the FSM (i.e., ACEs) or FIM (i.e., PCEs) can have important impacts on ERH and ECD.^68,70-2^ Such EBPIs often implicitly address both ACEs and PCEs, either by targeting ACEs that are barriers to PCEs (i.e., indirectly targeting PCEs), or by enhancing PCEs that have been shown to have reciprocal impacts on specific ACEs (i.e., indirectly targeting ACEs). For instance, the Family Check-Up home visiting program reduces maternal depression (ACE), which in turn increases supportive parenting (PCE), resulting in reduced child behavior problems.^72^ However, most such programs do not *simultaneously and directly* address ACEs and promote PCEs, and therefore may not be adequate to fully reduce disparities or comprehensively impact ECD, particularly for families with the fewest resources.^5,73^ *Theoretical and empirical considerations together, therefore, suggest that integrated EBPIs that target both ACEs and PCEs have the potential to address this gap*.

Thus, we hypothesize that the integrated HealthySteps (HS) and PlayReadVIP model (HS+PlayReadVIP) will promote early relational health and child development outcomes by simultaneously addresses ACEs and promotes PCEs, offering a comprehensive approach to supporting parenting and enhancing ECD outcomes.

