## Primary Objective

There are two primary objectives of this study:

**Aim 1. Implement the optimized integrated HS+VIP model (formalized in Aim 1), and conduct an effectiveness-implementation study (Hybrid I design).**

1. Examine effectiveness of the integrated HS+VIP model, including parent mental health, parenting behavior, and early child development outcomes.
2. Examine implementation outcomes, including reach, appropriateness, acceptability, feasibility, and fidelity, using an integrated RE-AIM^18^ and CFIR^19^ framework.

**Aim 2. Examine health disparities mechanisms underlying effectiveness-implementation outcomes.** Using a mixed methods design, we will examine whether HS+VIP impacts are 1) mediated by impacts on parent assets/vulnerabilities and ERH or 2) moderated by CFIR contextual factors or RE-AIM domains.

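### Testing 12-month mediators only one at a time cannot separate or apportion correlated pathways, so Aim 2 needs a joint mediator model beside the separate ones

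*Protocol*

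**What the plan says.** The protocol's mediation paragraph (Statistical and Analytical Plans, Mediation Through Intervention/Health Disparities Theory of Change) asks whether 24-month child outcomes result from 12-month effects on parents and ERH, "using SEM with bias-corrected bootstrapping". It then sets the rule: "Mediators will be examined separately". The same sentence adds a gate, under which a mediator is tested only if the program has a significant effect on it at 12 months. The document plans no parallel or serial multiple-mediator model and no contrast of indirect effects.

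Under Primary Objective, Aim 2 asks whether impacts are "mediated by impacts on parent assets/vulnerabilities and ERH". The Background section describes the purpose of Aim 2 as "examining the mechanisms driving its impacts and the contexts influencing its implementation".

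The Rationale links the mediators to one another. It describes the family stress and family investment models as interrelated and has them converge on ERH. It states that "ACEs negatively affect ERH and ECD through ecological factors and parenting capacities that are barriers to ERH", and it refers to programs "enhancing PCEs that have been shown to have reciprocal impacts on specific ACEs".

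**The concern.** The one-at-a-time rule is stated, so it is not a detail left open for an analysis plan. A plan that follows the protocol inherits it.

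The rule sits badly with the aim. If stress-side and investment-side mediators correlate within families, a model holding only one of them lets it stand in for the other. Each separate indirect effect then contains shared effect, so the separate estimates overlap and can be neither compared nor added. A mediator that the program moves, but that does nothing for the child outcome, can be reported as a mechanism because it travels with the one that does.

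The comparison of arms on effectiveness is untouched. At stake is the mechanism conclusion, which the protocol lists among its primary objectives and which bears on the trial's rationale of acting on adverse and positive experiences together.

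**Working it through.** **The plan's own figure.** Sample Size gives 500 enrolled, 400 analysed, d = .30, alpha .05 and more than 80% power. 500 × (1 − .20) = 400. With 200 per arm, z = .30 × √(400/4) = 3.0 and power is 85% (two-sided; 84.9% from the noncentral t). The figure reproduces.

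**Inputs for the mediation check**
- From the protocol: n = 400, about 1:1 allocation, alpha .05 (taken as two-sided), and the gate of a significant 12-month effect.
- Assumed: both mediators are moved by d = .30, which the protocol gives for main impacts and not for each mediator. M1 has a true path b1 = .3 to the child outcome. M2 is inert (b2 = 0). Residual SDs are 1. The mediators' residual correlation is r.
- Mediation is declared when both the program-to-mediator and the mediator-to-outcome paths are significant. This stands in for the bias-corrected bootstrap interval.

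**What the separate model estimates for M2.** With M1 left out, the slope of the outcome on M2 given arm is b1 × r, not 0. The residual variance is 1 + b1²(1 − r²), so z = b1·r / √{[1 + b1²(1 − r²)]/400}. The probability of declaring M2 is roughly the gate probability (.85) times the power for that slope.

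| r | slope .3r | z | power for slope | × .85 |
|---|---|---|---|---|
| .1 | .03 | 0.57 | .09 | 7.5% |
| .3 | .09 | 1.73 | .41 | 35% |
| .5 | .15 | 2.90 | .83 | 70% |
| .7 | .21 | 4.11 | .98 | 84% |

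Simulations agree: about 7%, 33-37%, 69-73% and 83-85%. With both mediators in one model the expected rate is .85 × .05 = 4%, and simulation gives about 4-5% at every r.

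**Size of the estimate.** M2's separate indirect effect is .30 × .3 × r. At r = .5 that is .045, half of M1's .30 × .3 = .09. In the joint model it averages 0.

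**Sensitivity**
- Weaker true path (.26): the separate models declare M2 in 28%, 61% and 80% of trials at r = .3, .5 and .7. In the joint model M1 keeps 83-85% power.
- Program barely moves M2 (d = .10): the gate is passed with probability .17. The rates fall to .17 × .41 = 7%, .17 × .83 = 14% and .17 × .98 = 17% at r = .3, .5 and .7; simulation gives about 7-16%.
- Program does not move M2: about .05 × .83 = 4% at r = .5.

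**Price of the joint model.** If both paths are real (.15 each), the chance of detecting both is about 71%, 73% and 79% with separate models at r = .3, .5 and .7, and about 48%, 35% and 16% jointly.

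**The case against.** Several objections stand and limit the point.

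- **Shared cause.** A reader might infer that the problem survives perfect control of confounding. It does not if the correlation comes from a common family cause: with adjustment for that cause, the separate models declare the inert mediator in only 4-5% of trials at every r from .1 to .7. Whether the planned sociodemographic covariates capture such a cause is unknown.
- **Serial chain.** A reader might call every detection of the second mediator false. If that mediator acts on the first, as the Rationale's path from assets and vulnerabilities through ERH to the child outcome has it, its indirect effect of .30 × r × .3 is real. The separate model estimates it correctly as a total indirect effect.
- **Order.** The theory does not settle the order by itself. The Rationale lets positive experiences be both ERH and underlying assets, describes reciprocal effects, and both sets of mediators are taken at 12 months.
- **The gate.** It protects when the program leaves a mediator unmoved. Both arms receive HealthySteps, whose reported effects are on family vulnerabilities, so stress-side mediators may differ little between arms.
- **Nearly always both.** A reader might infer that separate models would almost always support both pathways. In the unfavourable case above, both are declared together in 6%, 32%, 63% and 78% of trials at r = .1, .3, .5 and .7, and the protocol gives no correlation.
- **Wording of the aim.** Aim 2 asks whether impacts are mediated, and no section plans to rank or add indirect effects. But the stated purpose is to learn which mechanisms drive the impacts, and separate models alone cannot answer that once two correlated mediators pass the gate.

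**Conclusion.** The point holds in limited form. The stated rule lets the trial show that each mediator is compatible with mediation. It does not let it separate or apportion pathways when the program moves several correlated mediators.

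The size depends on three assumed quantities: the mediator correlation, the program's effect on the second mediator, and the true path. With d = .30 on both mediators and a true path of .3, misattribution is small at r = .1 and material from about .3. With d = .10 on the second mediator it stays at about 7-16% for r of .3 to .7. The figures treat the second mediator as inert and not upstream, and assume that its correlation with the first is not removed by covariates.

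The documents do not support the stronger conclusion that the separate models are worthless or should be replaced. With two real, highly correlated paths the joint model is the weaker detector. The effectiveness analyses are unaffected.

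**What to change.** Keep the separate models and add one prespecified SEM that holds jointly all the 12-month parent asset/vulnerability and ERH mediators that pass the 12-month gate. Report specific and total indirect effects. If the serial path from assets or vulnerabilities through ERH to the child outcome is fitted, label it as resting on the Rationale's theory, because both sets are measured at 12 months and timing does not fix their order.

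State that any claim about which pathway carries the effect rests on the joint model, and that separate indirect effects are not compared or added.

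The change needs only wording; data and software stay the same. The cost is lower power for each path when mediators are highly correlated and both real, so a null specific effect in that setting must not be read as absence of mediation. The joint model also still assumes no unmeasured mediator-outcome confounding, and the text should say so.

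### Testing only mediators with a significant 12-month arm effect overstates the indirect effects that are reported and leaves the other mediators without an indirect-effect estimate

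*Protocol*

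**What the plan says.** Aim 2 is one of the two primary objectives (Protocol, section 3.1). It asks, among other things, whether HS+VIP impacts are "mediated by impacts on parent assets/vulnerabilities and ERH".

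The mediation paragraph of section 9.1 relates 24-month child outcomes to 12-month effects on parents and ERH, "using SEM with bias-corrected bootstrapping". It continues: "Mediators will be examined separately", and "only mediators on which HS+VIP has a significant impact at 12M will be tested". It gives no threshold for significance and does not say whether the p-value is raw or adjusted.

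Three other places bear on this:
- Section 9.1, tests of hypotheses, plans intent-to-treat regressions of the outcomes at each assessment.
- Sections 9.4.4 and 9.4.6 plan a false discovery rate approach, for the 12-month analyses and for multiple comparisons in general.
- Section 9.5 gives the sample size: "With enrollment of 500 families, we expect a final sample size of 400", with "more than 80% power to detect an effect size of *d* = ~.3 given alpha = .05 in ANOVA analyses" and "80% power to detect a small-to-medium effect size (.26) in mediation analyses based on previous simulation studies".

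**The concern.** An indirect effect is the product of two paths: a (arm to 12-month mediator) and b (mediator to 24-month outcome, given arm). The gate keeps a mediator only when the estimate of a is large relative to its standard error. That same estimate then enters the product. Conditional on passing, the estimate of a is too large on average, and so is the indirect effect. The bootstrap resamples families within a mediator already chosen, so it does not undo the selection.

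Mediators that fall short get no b-path, no indirect effect and no interval. A reader of the Aim 2 results would see overstated effects for a partly chance-determined subset, and could take silence on the rest as evidence against them.

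Mediator effects below .30 are plausible on the protocol's own account, though this is an inference. The .30 is a planning value for main impacts, not for each 12-month mediator. The comparator is active: section 2.1 credits HealthySteps with effects on maternal depressive symptoms. The 12-month assessment falls at day 180 ± 90 (section 7.3.3), well before delivery ends. Arm differences on parent vulnerabilities could therefore be modest.

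**Working it through.** **Inputs from the protocol.** Final N = 400, about 200 per arm (section 9.5); alpha = .05 and d = .30 (section 9.5); mediation effect .26 (section 9.5, metric not defined, read here as an arm difference in SD units).

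**Assumptions.** Two-sided .05 gate on a raw p-value; unit-SD mediator; no covariates or measurement error. The 12-month N is not given. Attrition is stated only as a "cumulative attrition rate of 15-20% by 24M", so 400 to 500 is the range.

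**Step 1: the plan's own power.** The standard error of an arm difference in SD units is 2/√400 = 0.10. At d = .30, m = .30/.10 = 3.0, and power is Φ(3.0 − 1.96) = Φ(1.04) = 85% (noncentral t: 84.9%). The stated power of more than 80% is reproduced.

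**Step 2: effect of selecting on |z| > 1.96.** With m = d/SE, c = 1.96, and φ, Φ the normal density and distribution function:
- pass probability P = Φ(m − c) + Φ(−m − c)
- mean of the selected estimate divided by the truth = 1 + [φ(c − m) − φ(c + m)]/(m·P)

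Example at d = .20: m = 2.0, φ(0.04) = 0.3986, φ(3.96) ≈ 0.0002, P = 0.516; ratio = 1 + 0.3984/(2.0 × 0.516) = 1.386.

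| True a (SD) | Excluded, N = 400 | Overstated, N = 400 | Excluded, N = 500 | Overstated, N = 500 |
|---|---|---|---|---|
| .30 | 15% | 9% | 8% | 5% |
| .26 | 26% | 17% | 17% | 11% |
| .20 | 48% | 39% | 39% | 28% |
| .15 | 68% | 74% | 61% | 59% |

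From a = .40 upward the overstatement is about 1% or less.

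**Step 3: does it carry to the indirect effect?** In this linear model the errors in the two path estimates are independent, so the product inherits the ratio. Simulating the whole chain at N = 400 with b = .30 (assumed) gives gated ratios of 1.09, 1.17, 1.38 and 1.75 at a = .30, .26, .20 and .15. Without the gate the ratio is 0.99 to 1.02.

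**Step 4: would FDR at the gate cure it?** No. A Benjamini–Hochberg gate (q = .05, 5 to 10 mediators assumed) gives an overstatement of the a-path of 46–49% at a = .20 and 89–100% at a = .15. It also passes fewer modest mediators.

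**Step 5: false positives.** A mediator declared under the gate must both pass it and have an interval excluding zero, so gated declarations are a subset of ungated ones. Simulation of the bias-corrected bootstrap with a = 0, N = 400 and b = .10, .15, .26, .39 (1,500 runs each) gives errors of 6.0, 7.5, 6.8 and 5.3% ungated, against 3.7, 4.3, 5.0 and 4.3% gated. A repeat with 1,200 runs gave 4.1, 7.8, 6.9 and 5.9% against 2.8, 5.5, 4.7 and 4.9%. The gate lowers the error in every setting; without it the bootstrap is slightly liberal in most.

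**The case against.** **The harm is small at the design effect.** At d = .30, which the protocol calls conservative against earlier results of .3 to .5, the overstatement is 9% and 85% of mediators pass. The 39% and 74% need effects that the protocol does not state. This stands, and it limits the weight of the point.

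**The gate fits the question.** Section 9.1 asks whether 24-month changes result from 12-month impacts, so requiring a demonstrated impact is coherent. That justifies caution in declaring mediation. It does not justify leaving the indirect effect unreported or reporting a selected estimate as if it were unselected.

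**Gated-out mediators are not wholly unexamined.** The intent-to-treat regressions estimate the 12-month arm effects without selection. True: what is missing is the b-path, the product and its interval. Few detections are lost either. At a = .20, significant indirect effects occur in 51.9% of trials without the gate and 51.2% with it using a Monte Carlo product interval, or 55.7% and 50.3% using the bias-corrected bootstrap.

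**A stronger reading to avoid.** A reader might infer that multiplicity in the mediation analysis is uncontrolled, with each null mediator passing at 5% and, for 10 independent ones, a 1 − .95^10 = 40% chance of at least one passing. The protocol does not support this. It fixes neither a raw .05 threshold nor the number of mediators, it plans FDR in sections 9.4.4 and 9.4.6, and step 5 shows that the gate reduces false positives. With FDR at the gate, the all-null chance of any pass is about 4–5%. The most that can be said is that section 9.1 does not tie the mediation tests to that FDR.

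**Conclusion.** The point holds as a bias and reporting problem. Selecting on the 12-month arm effect and reusing it overstates reported indirect effects by about 9% at a = .30, rising to 74% at .15, and leaves 15% to 68% of real mediators of those sizes without an indirect-effect estimate or interval. FDR at the gate would not remove this.

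The sizes rest on N = 400, an assumed two-sided .05 gate and an assumed true arm effect on the mediator; they fall if the 12-month sample is larger. At the planned d = .30 the harm is small. It is not a finding of inflated type I error. The change is worth making because estimates of mechanism are what Aim 2 is meant to deliver and the remedy is cheap.

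**What to change.** In section 9.1:
1. Delete the clause "only mediators on which HS+VIP has a significant impact at 12M will be tested".
2. State that the a-path, the b-path and the indirect effect, each with an interval, will be estimated and reported for every 12-month parent asset/vulnerability and ERH mediator, whatever the significance of the arm effect.
3. State that the FDR of section 9.4.6 covers the indirect-effect tests. This matters more once the gate is gone, because the gate was offsetting the slight liberality of the bias-corrected bootstrap. FDR handles the number of tests; it does not itself correct that liberality.

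Cost: a few more models, no new data or participants, and a slightly harder claim for each single mediator.
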